### Aims

While the Housing First approach has been evaluated internationally [27,20,28,29] and is being keenly applied in Australia, there has been a paucity of evidence on the effectiveness of Australian adaptations of the approach. Findings from evaluations of individual Housing First programs within Australia have recently been released publicly [30,31], however no study examining more than one of these adaptations with the same methodology has been conducted. Further, evaluations to date have focused largely on housing sustainability rather that incorporating broader measures of health and quality of life. Given this, there remains a pressing need to determine the efficacy of these respective models (Platform 70 [scatter site]; Common Ground [congregated site]) in relation to both housing and health outcomes. In response to this gap in the evidence-base, we have commenced a longitudinal analysis of these two adaptations using a standardised mixed methods approach to examine the changes in housing and health outcomes associated with the respective models.

Specifically, we aim to:Determine whether changes occurred with respect to clients’ housing stability, physical and mental health and treatment rates, psychological distress, quality of life, substance use patterns, and health and criminal justice system contact.Identify the demographic and social characteristics of clients that predicted success in each model. For the purposes of this study, success was defined as sustained tenancy and improved health and well-being outcomes.Calculate the net of ‘cost offsets’ of the two programs; that is, the reduction in measurable health, criminal justice and other costs borne by government as a consequence of the program.

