#### Housing and support program data

Program data was accessed for the cost analysis. Of all consenting participants, a breakdown per month of their rental arrears, the arrears escalation pathway undertaken by staff, and tenancy damages were extracted. De-identified program data of all clients was also obtained, which included the duration and intensity of support services received (housing case management and health services) and tenancy stability indicators such as the total number of days housed, frequency of housing transitions since first being housed by the program, and number of neighbour complaints during the evaluation timeframe. Agencies providing support and tenancy management to clients as well as community housing providers were interviewed to ascertain the costs of program provision.

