### Data analysis

Given the nature of the housing programs under evaluation, we were limited by the number of clients engaged with each program and therefore did not perform a formal power-based sample size calculation. Instead, we invited all eligible Platform 70 and Common Ground clients to participate in the client survey, and recruitment continued until all eligible clients had either provided consent or declined participation in the research.

Loss to follow-up comparisons that assesses the characteristics of participants in the two programs who completed both baseline and follow-up client surveys (completers) against those who only completed the baseline survey (non-completers) will be made. The purpose of these comparisons is to determine whether there are any key differences between survey completers and non-completers of each program. Other patterns of missing data will be examined to determine if there are potential biases. Appropriate literature that addresses how to deal with missing data and small populations and/or small samples will also be consulted.

To address Aims 1 and 2, a profile of clients engaged with the two housing programs will be constructed, which will include demographics, homelessness history and health status. Multivariate analysis will be undertaken to determine changes over time (baseline to follow-up) in key outcomes, including housing, health status and treatment rates, quality of life, substance use patterns, and contact with the health and criminal justice systems within and across the two programs. Additionally, multivariable logistic regression will be used to identify factors associated with sustained tenancies using SAS version 9.4 software.

Qualitative interviews with clients and stakeholders will be thematically analysed in line with the general inductive approach using NVivo 10 software. The analysis will identify key themes in sustained and failed tenancies. These data will be presented in such a way as to give some indication of the commonality or otherwise of particular views, but will not purport to be representative.

To address Aim 3, the cost to government of mainstream health and criminal justice service use by Platform 70 and Common Ground clients and how this use changed over time will be examined. It will also review the cost of delivering the programs and the extent to which this is offset by a decrease in the cost of mainstream government services use by participants.

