A detailed examination of mainstream services will utilise the health and criminal justice system contact data collected in the client surveys. Associated costs incurred in the 12 months prior to the baseline client survey will be compared with the cost of services used in the 12 months prior to the follow-up client survey. The cost of health and justice services will also be compared with the NSW population average.

The cost of health and justice services used by client survey participants will be estimated by applying the unit cost for each service to reported use. Unit costs will be estimated from publicly available information including the Report on Government Services 2013 [42] and various other reports, including those published by the Australian Institute of Health and Welfare [43-47]. These sources will also be used to estimate average service use and associated cost for the NSW population.

The cost of delivering the Platform 70 and Common Ground programs will be examined with reference to recurrent expenditure for the period in which clients were housed in the program. We shall also consider the range of rental subsidies provided to clients in the two housing models. Funding and expenditure data will be sought directly from the providers of social, health and tenancy management, and administrative services. To estimate the recurrent cost incurred by housing providers to manage and maintain properties, we shall draw on estimates obtained from the Report on Government Services [42]. Platform 70 and Common Ground case workers potentially provide more time to resolving issues associated with their tenancies than is normal. This implies that the average recurrent cost/dwelling is likely to represent a conservative estimate of the cost incurred by housing providers.

Housing providers also incur the capital cost of accommodation. In our cost analysis we will only consider public and community housing capital costs in the Common Ground program as Platform 70 involves the head leasing of privately owned dwellings. The average capital value of public housing and community housing properties available to Common Ground clients will be established and the annualised value of capital employed estimated by applying an opportunity cost of capital of 8% [42] to the average capital value.

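### Aim 3 costs property management and maintenance at a sector average that the plan expects to be low; the plan calls this conservative, but it overstates the net saving

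*Protocol article*

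**What the plan says.** The third aim (Aims) is to "Calculate the net of ‘cost offsets’ of the two programs". The Data analysis section puts this into practice by reviewing what the programs cost to deliver and "the extent to which this is offset by a decrease in the cost of mainstream government services use by participants".

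Program cost comes from several sources:

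- **Support, tenancy management and administration:** "Funding and expenditure data will be sought directly from the providers of social, health and tenancy management, and administrative services".
- **Housing providers' recurrent cost of managing and maintaining properties:** "we shall draw on estimates obtained from the Report on Government Services".
- **Capital:** an 8% opportunity cost on average capital value, for Common Ground alone, because Platform 70 head-leases private dwellings.

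On the second item the article adds that "Platform 70 and Common Ground case workers potentially provide more time to resolving issues associated with their tenancies than is normal", and then: "This implies that the average recurrent cost/dwelling is likely to represent a conservative estimate of the cost incurred by housing providers".

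Earlier, under Housing and support program data, it reports: "Agencies providing support and tenancy management to clients as well as community housing providers were interviewed to ascertain the costs of program provision".

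**The concern.** In an economic evaluation, a conservative assumption is normally one that works against the conclusion the program would like to reach. Here the assumption works in the program's favour. The plan gives a reason to think one cost item is too low, gives it a reassuring label and carries it into a net figure without an upward case. A policy reader who sees the word could take the net offset to be a cautious figure when, on the plan's own premise, it leans towards showing that the programs pay for themselves.

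The plan also appears to have better information for at least part of this item. Community housing providers were interviewed about costs, and tenancy management expenditure is to be requested from providers. The article does not say how those sources relate to the published average, or which takes precedence where they overlap.

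**Working it through.** The article states no cost, offset or unit value for Aim 3, so there is no figure to reproduce. The check is of direction, followed by an illustration on assumed inputs.

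**1. Structure, from Aims and Data analysis**

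Net offset = (service cost before − service cost after) − (S + R + H)

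- S = support, tenancy management and administration, sought from providers.
- R = recurrent cost to manage and maintain properties, taken from the published average.
- H = cost of the dwelling itself (annualised capital, or head-lease rent).

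**2. Direction**

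Let the true recurrent cost be R × (1 + u), with u > 0 as the plan expects. Using R in its place gives:

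Stated net offset − true net offset = R × (1 + u) − R = R × u > 0

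The overstatement passes one for one into the net offset. The stated reason covers both programs, so both offsets are affected.

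**3. Comparison between programs**

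If R is the same in both, the bias in the difference between the two net offsets is R × (u for Platform 70 − u for Common Ground). It vanishes if the extra workload is equal. The article gives no basis for saying which is larger, so this component does not show a tilt towards either model.

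**4. Illustration (R and u are assumptions, in AUD per dwelling-year)**

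| Assumed R | u = 10% | u = 25% | u = 50% |
|---|---|---|---|
| 5,000 | 500 | 1,250 | 2,500 |
| 7,500 | 750 | 1,875 | 3,750 |
| 10,000 | 1,000 | 2,500 | 5,000 |

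For example, 10,000 × 0.50 = 5,000.

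**5. Capital rule, checked separately**

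The charge is 0.08 × V, where V is the dwelling value, which the article does not give. For an assumed V of AUD 200,000 to 500,000 it is 0.08 × 200,000 = 16,000 to 0.08 × 500,000 = 40,000 per dwelling-year. This adds to Common Ground's cost and so lowers its net offset. It is a gross charge and does not measure bias. Any imbalance between the models would be this charge less whatever head-lease rent is counted for Platform 70, which could be near zero.

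**The case against.** **The label is correct for its object.** The sentence calls the average a conservative estimate of the providers' cost, and a low figure for a cost is commonly described that way. Nowhere does the article claim that the net offset is conservative, and it discloses the likely direction of the error. This stands as a reading of the sentence. It does not remove the effect on Aim 3, which reports the net figure.

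**Only one component is involved, and the text is hedged.** The excess is put as possible and the understatement as likely. Social, health, tenancy management and administrative costs are to come directly from providers. The extra time is attributed to case workers, so some of it may already be in those data. This also stands: the shortfall is confined to whatever the direct data do not capture. A reader might infer that program cost as a whole rests on an admitted underestimate, but the article does not support that.

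**The capital rule is reasoned.** A reader might infer from "we will only consider public and community housing capital costs in the Common Ground program" that the rule flatters the net offset or makes the scatter-site model cheaper by construction. Neither follows. The charge works against Common Ground. For Platform 70, rent paid to a private owner already pays for the owner's capital, and a further charge would count it twice. Platform 70 would look too cheap only if head-lease rent were left out, and nothing in the article says that it is. The section on the scatter-site program describes government funding for the head leases, the Abstract says rental subsidy data will be used in the economic evaluation, and Data analysis costs delivery from recurrent expenditure while clients were housed. The article does not say outright that the full rent is counted, which calls for a clarifying sentence and no more.

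**This is a condensed article.** Rules for netting client rent or allocating upkeep can reasonably sit in a fuller costing plan, and their absence is not held against it. The sector-average rule and its label are in the text shown.

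**Conclusion.** The point holds for one cost component. If the plan's own premise is right, costing property management and maintenance at the sector average overstates the net offset of both programs by the full amount of the shortfall. For Aim 3's output the estimate is therefore anti-conservative, and the article states no upward case to offset it.

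The direction follows from the definition of the net offset and needs no outside figure. The size cannot be derived from the documents. The range of AUD 500 to 5,000 per dwelling-year rests wholly on the assumed R and u, and would be smaller to the extent that provider data already capture the extra time.

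The difference in capital treatment between the two models is not a fault in itself, and no bias in favour of Platform 70 is shown.

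**What to change.** 1. Where they are available, use as the base case the costs providers reported at interview and the tenancy management expenditure requested from them. State which source covers which activity, so that nothing is counted both there and in the published average.
2. Keep the published average as a lower-bound cost case, and add a sensitivity case above it.
3. Replace the description of the average as conservative with a statement that it probably understates program cost and so biases the net offset in the programs' favour.
4. As a clarification, state that Platform 70's head-lease rent is counted in program cost as the counterpart of Common Ground's annualised capital charge.

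The cost is a few sentences of costing rules and one additional scenario. The interviews have been done and expenditure data are already being sought, so no new collection should be needed where those responses are usable. The drawback is that the stated net saving may become less favourable.

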## Discussion

### Contributions

Given the chronicity of homelessness in Australia, a novel housing policy approach to reducing homelessness has been recently introduced. The housing programs are based on the Housing First approach, whereby individuals who are chronically homeless are offered a tenancy, without first having to be housing-ready. This study will address an important gap in both the public health and housing literature by examining the nature and extent of changes for clients upon being placed in one of the two variations of the Housing First approach; Platform 70 (scatter site model) or Common Ground (congregated model). Additionally, this study will document the journeys of a sample of people in the programs by recording their individual changes over time as they are placed into one of the long-term housing programs available.

Housing and health are inextricably linked and evaluations of housing policy should measure outcomes across both domains. Whilst randomised controlled trials are the gold standard approach for much health research, they are not the most appropriate methodology when assessing the impact of programs that deliver housing and the denial of the intervention (housing) to a control group is not an option. In this situation, a longitudinal mixed-methods approach using standardised and validated measures is appropriate.

### Strengths and limitations

A key strength of this study is that it is uniquely positioned to provide robust evaluative evidence of the efficacy of these housing programs within an Australian context. The timing of this study is particularly critical due to the recent rapid development of Common Ground buildings throughout Australia, despite the lack of published empirical research to support the expansion of the model [26]. A further strength of the methodology is the extensive recruitment and follow-up procedures in place. The success of these procedures to recruit and follow-up with transient clients will provide a template for future research with vulnerable and homeless populations.

It is important to acknowledge the limitations of this evaluation. First, individuals housed through these programs had chronic homeless histories and were identified as requiring priority housing due to their high level of vulnerability. Subsequently, the findings have limited generalizability to the full homeless population in Sydney. Second, the methodology is mostly reliant on self-report measures, which may affect reporting accuracy due to factors such as memory error, nondisclosure, social desirability or intentional misrepresentation [48]. To reduce the chance of this occurring, a recall timeframe of 12 months or less and visual show cards were used, as were standardised tools validated for use with vulnerable populations [49]. It was noted during the study design that previous studies have demonstrated a moderate to high internal consistency in self-reports by individuals experiencing homelessness, including those with severe mental health conditions [50,51]. Additionally, all participants were informed that their client surveys and qualitative interviews were confidential and their responses would not affect their relationships with housing or support services. The final limitation is the small sample sizes. However, the nature of the programs means that the population from which to recruit from was also small. Despite this, substantial time and resources were devoted to contacting every eligible client to ensure that everyone had an opportunity to participate, including going on street patrols and spending days shadowing case managers. Significant efforts have also been made to identify appropriate analytical techniques for small samples.

## Conclusion

This study is the first to utilise a standardised mixed methods approach to simultaneously evaluate two adaptations of the Housing First approach in Australia. This extends previous work that has focussed largely on housing sustainability as the outcome. This research has the capability to contribute substantially to both public health and housing policy realms, and is significant in its timing given the rising rates of homelessness and expansions of similar housing programs in Australia and worldwide.
